In addition to aerobic exercise, research based on mind-body therapy have also achieved preliminary results in improving cognitive function among cancer patients [25–27]. In breast cancer survivors, mindfulness-based exercise may be superior to gentle exercise or survivorship support in terms of improving self-reported cognitive function and distress [25]. Oh et al. [26] demonstrated that a 10-week medical Qigong program significantly improved subjective cognition with medium effect size. Baduanjin, a traditional Chinese fitness exercise combining meditation and repetitive movement with low intensity [28, 29], is considered to be an effective exercise in promoting health [28]. Recently, a review [30] supported that Baduanjin exercise may be effective as an adjunctive rehabilitation method for improving cognitive function, but the effect of Baduanjin exercise on CRCI needs to be further explored.

Therefore, the primary purpose of this article is to describe the protocol of a randomized control trial to examine whether Baduanjin exercise program is a protective measure in improving cognitive function in chemotherapy-exposed patients with early-stage breast cancer.

The main aims of the trial are as follows:
Whether a 3-month Baduanjin intervention improves subjective and objective cognitive function of breast cancer patients during chemotherapyWhether a 3-month exercise intervention improves quality of life and cancer-related symptoms such as fatigue, depression, and anxietyWhether there is an association between subjective or objective cognitive function, symptoms, and quality of life

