### Randomization and blinding

Participants will be randomly assigned to 1 of 2 groups—an intervention group or a control group—in a 1:1 ratio using the SPSS 24.0 software. The allocation of the result will be put into sealed, opaque envelopes by a study administrator not involved in the study, and the group numbers will be subsequently disclosed. Given that Baduanjin exercise is a well-known exercise to the study population, blind method is conducted to assessors only, not physicians or patients. In addition, all participants will be asked not to discuss the practice with each other to minimize bias. The assessor will also be instructed not to acquire the participant’s exercise information. Participants are allowed to withdraw without giving a reason at any time. If any patient experiences adverse effect during exercise, such as palpitation or severe upper limb lymphedema, but still wishes to participate, there will be a therapist available who will evaluate whether the patient can continue on the study.

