### Patient-reported outcomes

Patients will complete several patient-reported outcome questionnaires aimed to evaluate subjective fatigue (Chinese version of the Multidimensional Fatigue Symptom Inventory-Short Form (MFSI-SF-C) [38]), mood (Hospital Anxiety and Depression Scale (HADS) [39]), and health-related quality of life (Functional Assessment of Cancer Therapy-Breast (FACT-B) [40]) (see Table 2).

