### Sample size

The sample size was estimated in this study by using perceptive cognitive impairment as the main effect indicator, which refers to the results of Oh et al. [26]. Using the G*Power 3.1 software, 58 cases of the total sample can be calculated with a test power of 0.80. Considering the 20% dropout rate, the total sample size for this study is about 70 patients randomized to the intervention group or the control group.

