### Data analysis

Demographics and other characteristics will be reported descriptively to summarize the distribution of all variables via the statistics software (SPSS 24.0). The means and SD will be calculated for continuous normally distributed variables and medians and ranges for non-normally distributed variables. Categorical variables will be presented by absolute numbers and percentages. All cases for both baseline and follow-up measurements will be analyzed for the different outcomes. If missing values exceed 10%, we will impute missing values on covariates by using multiple imputation.

According to the intention-to-treat principle, we will compare the number of patients showing post-intervention 7-point improvement in the PCI scores between the intervention group and the control group using Fisher’s exact tests. A linear mixed-effect model for repeated-measures analysis will be used to analyze the changes in cognition such as treatment, time point, and the interaction between treatment and time point. The between-group effect size will be calculated in post-treatment means (dividing the between-group difference with the pooled standard deviation). The effect sizes of 0.20, 0.50, 0.80, and 1.30 represent small, medium, large, and very large effect, respectively [41]. Two-sided significance level for all tests is 0.05.

Linear regression analysis adjusted for baseline will be used to assess the association between changes in cancer-related symptoms (fatigue, anxiety, and depression) and changes in cognitive function. Adherence to the Baduanjin exercise will be noted by adherence rate ((total frequency − absenteeism)/total frequency × 100%).

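### The Aim 3 regression names baseline as its only adjustment and omits quality of life: read as written, a treatment effect on both symptoms and cognition would feed into their estimated association, and part of the aim has no stated analysis

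*Protocol article*

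**What the plan says.** The third aim at the end of the Background section asks whether "there is an association between subjective or objective cognitive function, symptoms, and quality of life". It therefore names three domains: cognition, symptoms and quality of life.

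The Data analysis section of the same article answers with a single sentence: "Linear regression analysis adjusted for baseline will be used to assess the association between changes in cancer-related symptoms (fatigue, anxiety, and depression) and changes" (the latter being cognitive change). The symptom list is given in brackets and holds three items. Baseline is the only adjustment mentioned.

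One paragraph earlier, the same section describes the linear mixed model as analysing "the changes in cognition such as treatment, time point, and the interaction between treatment and time point". Treatment is thus named as a term for that model and not for the regression.

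The Patient-reported outcomes section lists FACT-B as the measure of health-related quality of life, so the data needed for the rest of Aim 3 will exist. The significance rule is general: "Two-sided significance level for all tests is 0.05".

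**The concern.** Two things do not fit together.

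First, Aims 1 and 2 suppose that the exercise improves cognition and also improves fatigue, depression and anxiety. If it does, randomised arm is a common cause of both change scores. A regression across both arms without an arm term mixes two sources of association: how symptom change and cognitive change go together among patients treated alike, and the fact that the two arm means differ on both. Adjusting for baseline does not remove the second source, because randomisation makes arm independent of baseline in expectation. The risk is that a paper reports symptoms and cognition as moving together in patients when all that happened is that the intervention moved each of them.

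Second, the stated regression has no quality-of-life variable. The links between cognition and quality of life, and between symptoms and quality of life, are in the aim but in no stated analysis.

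**Working it through.** **Quality of life.** No arithmetic is needed. Aim 3 lists cognition, symptoms and quality of life. The regression sentence lists fatigue, anxiety, depression and cognitive function. FACT-B is collected. Of the three pairs of domains in the aim, one (symptoms with cognition) has a stated analysis and two have none.

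**Arm term: inputs.**
- Allocation is 1:1 (Randomization and blinding section).
- The test is two-sided at 0.05 (Data analysis section).
- The Sample size section says "58 cases of the total sample can be calculated with a test power of 0.80" and "Considering the 20% dropout rate, the total sample size for this study is about 70 patients". The article gives no figure for the Aim 3 regression itself, so there is none to reproduce.
- Evaluable patients: 70 × (1 − 0.20) = 56, or 28 per arm.
- Effect size: none is stated. Solving a two-sided t-test with 29 per arm and 80% power gives d = 0.749, so about 0.75 is the effect that 58 patients can detect. This is back-solved and is used only to place the range.
- Assumed: the same standardised benefit d on both changes, unit within-arm variance, no within-arm correlation.

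**Induced correlation.** With equal arms, the difference in arm means adds d²/4 to the variance of each change and d²/4 to their covariance. So

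r = (d²/4) / (1 + d²/4).

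- d = 0.3: 0.0225 / 1.0225 = 0.02
- d = 0.5: 0.0625 / 1.0625 = 0.06
- d = 0.75: 0.1406 / 1.1406 = 0.12
- d = 1.0: 0.25 / 1.25 = 0.20

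If only one outcome responds, the covariance term is d × 0 / 4 = 0 and r = 0.

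**Rejection rate of the nominal 5% test, 28 per arm, 20,000 simulated trials per scenario.**

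| Effect on both changes | No arm term | Arm term added |
|---|---|---|
| d = 0.5 | about 7% | about 5% |
| d = 0.75 | about 15% | about 5% |
| d = 1.0 | about 32% | about 5% |

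At d = 0.3, or with d = 0.75 on one outcome and 0 on the other, the rate without an arm term stays near 5%.

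A hand check by Fisher's z agrees. At d = 0.75, atanh(0.1233) × √(56 − 3) = 0.124 × 7.28 = 0.90. The upper-tail probability beyond 1.96 − 0.90 = 1.06 is about 0.145, and the lower tail adds about 0.002, giving 0.147.

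**Sensitivity to the baseline adjustment.** The table has no baseline covariates, but the planned regression has them. A second simulation (10,000 runs) adjusted for both baselines, with a baseline to follow-up correlation of 0.5. The within-arm variance of each change is then 2 × (1 − 0.5) = 1 before adjustment and 1 − 0.5² = 0.75 after it. The induced correlation becomes (d²/4) / (0.75 + d²/4): 0.08, 0.16 and 0.25 at d = 0.5, 0.75 and 1.0. With N = 58 the rates are 8.7%, 21.6% and 48.5%. At d = 0.3 the rate is 5.7%, and with one outcome responding it is 5.2%. With an arm term all scenarios lie between 4.4% and 5.4%, counting the runs at N = 70. The pattern is the same and the size moves with the assumptions.

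**The case against.** The strongest reply is that the article never says the arms are pooled. It does not say whether the regression is run across arms, within each arm or with an arm term, nor which change is the dependent variable. The Trial monitoring section refers to a statistical analysis plan that is not shown and could contain the full model. This stands as a limit. A reader might infer that the protocol commits to a pooled, arm-free model, and the text does not support that. What remains is that the sentence names one adjustment, while the same section names treatment for the mixed model. The model an analyst would fit from that sentence has no arm term.

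A second reply is that the overall association among trial patients is real if treatment moves both outcomes, so detecting it is no error. This also stands in part: Aim 3 does not say whether it means the overall or the within-arm association. A reader might take the 7%, 15% and 32% as the true type I error of the planned test. The documents do not support that reading. The figures count as false positives only for the within-arm question, and they need equal effects on both outcomes, no within-arm association and an effect size the article does not give. The Background itself suggests that fatigue and negative emotions may contribute to cognitive impairment, so a within-arm association may well exist. The slope would then still carry the treatment effect, but a rejection would not be false. The Background also describes the study used for the sample size as showing a medium effect on subjective cognition, and the Data analysis section sets medium at 0.50, where the inflation is small.

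Neither reply touches the quality-of-life gap. There the article states its analysis and closes the list of variables, and the list does not match the aim.

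**Conclusion.** The point holds in two parts of different firmness. That quality of life is named in Aim 3, is measured, and has no stated association analysis is plain from the text. That a treatment effect on both symptoms and cognition would contribute to the estimated association holds on the natural reading of the regression sentence, which is an inference from the single adjustment named. The mechanism is sound, but its size is not known. Under the illustrative assumptions it runs from nothing (d = 0.3 or one outcome responding) through small (d = 0.5) to material (d = 0.75 and above). Aim 3 is secondary. The PCI comparison, the Fisher test, the mixed model and the sample size are unaffected. The change is worth making because it is cheap and because the confusion is greatest when the intervention works.

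**What to change.** In the Data analysis section, state that every Aim 3 regression includes randomised arm as a covariate as well as baseline, so that the coefficient estimates the within-arm association. An arm-by-symptom interaction can be examined as an optional check that the slope is similar in both arms.

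Add change in FACT-B to the set of associations, with cognition and with symptoms. If the investigators do not want those analyses, narrow Aim 3 to symptoms and cognition.

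The cost is a sentence or two of text, one degree of freedom per model and one extra set of regressions on data already being collected. No change to recruitment, assessments or the primary analysis is needed.

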### Dissemination

The findings of this study will be reported in a master’s thesis by the main author and submitted to a peer-reviewed journal for publication. It will be presented at relevant conferences on the subject of matter if possible.

## Discussion

Currently, although cognitive decline is a well-known phenomenon, there are no pharmacological interventions to prevent or alleviate cognitive problems in patients with various non-central nervous system cancers. Physical exercise has been recommended as a part of rehabilitation, which appears to be a feasible and promising non-drug intervention that improves cognitive abilities. Preclinical study [42] has shown that low-intensity exercise may assist in preventing cognitive dysfunction in chemotherapy-exposed patients with breast cancer. Baduanjin exercise as a mind-body therapy has beneficial effects on fatigue, quality of life, and negative mood among patients [30, 43, 44]. In addition, this kind of exercise is easy to learn and can be widely used in the community with no limitation for the environment [45]. Meanwhile, there is evidence demonstrating improved attention of the elderly or patients with MC [46, 47]. In light of the previous literatures, we hypothesized that the exercise program may have a protective effect on the cognitive function of breast cancer survivors. Given ethical reasons, patients assigned into the control arm have the opportunity to carry out a 3-month exercise program after completion of the study, so as to decrease subsequently the risk of sample contamination. If Baduanjin exercise seems to be effective, it may provide evidence-based intervention during cancer treatment to possibly minimize or decrease cognitive problems, thereby improving patients’ quality of life. Previous preclinical and human studies have shown that a wider range of chemotherapy was associated with cognitive changes in cancer patients, so we hope that the results of this study will also be applicable to patients with other types of tumors during receiving chemotherapy. Therefore, the ultimate purpose of this study may have a positive impact on the quality of life or physical and mental health of the growing survivors with cancer.

## Trial status

Recruitment of patients started on 1 June 2020. The trial is currently underway and expected to be completed by 1 June 2021. The protocol is 1.0 version. The date of edition was 22 May 2020.

## Data Availability

Data sharing is not applicable to this trial as no database is generated or analyzed for the current study.

## Abbreviations

FACT-Cog: Functional Assessment of Cancer Therapy-Cognitive Function
PCI: Perceived cognitive impairment
PCA: Perceived cognitive ability
HVLT-R: Hopkins Verbal Learning Test-Revised
TMT: Trail-Making Test
DSST: Digit Symbol Substitution Test
MFSI-SF-C: Chinese version of Multidimensional Fatigue Symptom Inventory-Short Form
HADS: Hospital Anxiety and Depression Scale
FACT-B: Functional Assessment of Cancer Therapy-Breast
SAE: Serious adverse event
TOC: Trial Oversight Committee
